### Nurses

Since the SELF-program is directly pointed at nurses, this participant group is considered the primary target group. The primary outcome for nurses, i.e. the level of stimulation behavior of self-reliance in ADL among geriatric clients, will be assessed at baseline (before implementation of the SELF-program; T0), directly after implementation of the SELF-program (approximately 3 months after the baseline assessment; T1), and 9 months after the baseline assessment (T2). The validated self-report MAINtAIN questionnaire will be used to assess the primary outcome measure [42]. The MAINtAIN comprises three subscales with a total of 19 items, representing whether nurses stimulate clients in a variety of daily activities, that can be rated on a 9-point Likert scale, ranging from ‘never’ to ‘always’. Of the 19 items, 8 deal with encouraging ADL, 6 with encouraging instrumental ADL and 5 with encouraging general function and physical activity. The 8 items focusing on encouraging ADL will be used as a the primary outcome.

Demographic characteristics of nursing care professionals will be assessed at baseline only. These include the participants’ gender (male, female or open answer option), age, education level (low; no education up to lower technical education, medium; general secondary education up to secondary vocational education or high; school of higher general secondary education up till university degree), nursing profession (nursing aide, certified nursing assistant or registered nurse), years of working experience in nursing care and within the current care setting, and number of working hours according to contract.

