### Sample size calculation

Given the cluster-randomized trial design, the guidelines prescribed by Breukelen and Candel (2012) were applied for sample size calculation (N) [44]. The SELF-program is expected to induce a difference in groups’ averages of the primary outcome (the MAINtAIN-score), corresponding to a small to medium effect size of 0.4 (Cohen’s *d*). Further, the mean cluster size, i.e. the average number of nursing care professionals per ward, is estimated to be 15. Using the two-tailed t-test, with power and significance level of 80% and 5%, respectively, the required number of clusters (K) was then computed, using an interclass correlation coefficient of 0.05 to correct for the cluster-randomized design effect (DE), yielding K ~ 8. Subsequently, K was increased in 10% to adjust for differences cluster sizes, and the associated sample size was further augmented to account for a 20% attrition of care professionals between baseline and post-treatment. This yielded a total sample size of *N* = 330 (165 per arm) care professionals and geriatric clients in K = 22 nursing home wards, or 11 ‘dyads’. In order to achieve adequate participant enrolment, we aim to include > 22 nursing home wards.

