### Data analyses

#### Effect evaluation

Summary statistics of central tendency (mean, median) and dispersion (standard deviation, interquartile range) will be used for continuous variables, as appropriate, to describe the two groups, whereas categorical variables will be summarized by absolute count and relative percentages (%).

Effect evaluation will be conducted according to the intention-to-treat principle with mixed (multilevel) linear regression analyses to accommodate the hierarchical structure of the data: measurements are nested within individuals, which are nested within a ward. Both wards and subjects will constitute the random effects (three-level models). Treatment, time and, their interaction, capturing treatment vs. control average differences over time, will make up the relevant fixed-effects, together with background characteristics that will be included in the model as covariates. Outcomes will be standardized to be interpreted as effect sizes (Cohen’s *d*). The regression coefficient of the treatment*time interaction in the mixed linear regression analysis can, therefore, be interpreted as Cohen’s *d*. To establish which factors are linked to (a possible) differential attrition between the groups, a logistic regression analysis with be conducted. SPSS for Windows, version 27 will be used for all statistical analyses. The level of statistical significance will be set at 0.05 (using two-tailed tests). In case of significant interactions, subgroup analyses will be conducted to determine the differential effects. In case of unintended effects due to the intervention or due to the trial conduct, these will be reported accordingly.

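### Read as Cohen's d, the treatment*time coefficient has the wrong unit if time is linear, and is two unranked contrasts if time is categorical

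*Protocol article*

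**What the plan says.** Under Data analyses, Effect evaluation, the protocol fits a three-level mixed model with treatment, time and their interaction as fixed effects, plus background covariates. Outcomes are standardized, and from this the section concludes: "The regression coefficient of the treatment*time interaction in the mixed linear regression analysis can, therefore, be interpreted as" Cohen's d. It refers to one coefficient. It does not say whether time enters as a number or as a category. On testing it says: "The level of statistical significance will be set at 0.05 (using two-tailed tests"), with no ranking of visits.

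The section on nurses under data collection gives the follow-up visits for the primary outcome as "approximately 3 months after the baseline assessment; T1), and 9 months after the baseline assessment (T2"). With baseline, that makes three measurements. The same section fixes the 8 ADL items of the MAINtAIN as the primary outcome and calls nurses the primary target group. Clients are measured at 0, 3 and 6 months.

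The sample size section works with a difference between group averages "corresponding to a small to medium effect size of 0.4" and inflates the sample "to account for a 20% attrition of care professionals between baseline and post-treatment". It does not name the visit to which the 0.4 applies.

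**The concern.** Standardizing an outcome fixes the unit of the outcome only. It does not turn a time interaction into a difference between groups. With two measurements coded 0 and 1, the interaction coefficient would be a standardized difference and the sentence would be right. With three, it depends on how time is entered:

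- **Linear time** gives one coefficient, which fits the singular wording, but its unit is SD per unit of time.
- **Categorical time** gives two coefficients, one for T1 and one for T2, so the sentence does not say which of them is d.

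Two things are at stake. Readers will compare the reported d with the planned 0.4, and under linear time the two are different quantities. An effect that appears at the end of training and then fades is also a realistic result: training lasts three months, T1 follows it directly, and the program has a session and nurse champions meant to maintain the behavior. A straight line over three visits is poorly suited to detecting that pattern.

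**Working it through.** **1. The plan's own figure.** The sample size section states: "Using the two-tailed t-test, with power and significance level of 80% and 5%, respectively". The effect is 0.4, the cluster size 15 and the intraclass correlation 0.05.

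- Per arm without clustering: 2 × ((1.960 + 0.842)/0.4)² = 98.1.
- Design effect: 1 + 14 × 0.05 = 1.7.
- Wards per arm: 98.1 × 1.7/15 = 11.1, where the section has K of about 8.
- From K = 8 onward the chain reproduces: 8 × 1.10/0.80 = 11 wards per arm, 11 × 15 = 165 nurses per arm, 330 in total.

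That K of about 8 does not reproduce is a separate matter, and nothing below rests on it. What matters here is that each step treats 0.4 as a standardized difference between two means. No slope and no unit of time enters.

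**2. Linear time.** For balanced data with random ward and nurse intercepts, the interaction coefficient is b = Σ(t − t̄)D / Σ(t − t̄)², where D is the true standardized arm difference at each visit. The denominator is 1 + 0 + 1 = 2 for coding 0/1/2, and 16 + 1 + 25 = 42 for months 0/3/9 (mean 4).

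| True difference at T0, T1, T2 | Coding 0/1/2 | Months 0/3/9 |
|---|---|---|
| 0, 0.4, 0.4 (sustained) | 0.4/2 = 0.20 | 1.6/42 = 0.038 |
| 0, 0.4, 0.2 (partial fading) | 0.2/2 = 0.10 | 0.6/42 = 0.014 |
| 0, 0.4, 0 (T1 only) | 0/2 = 0.00 | -0.4/42 = -0.0095 |

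The sustained slope per month amounts to 0.038 × 9 = 0.34 over the whole follow-up.

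**3. Power.** Assumptions: equal correlation r = 0.5 between visits, ward effects constant over time, and 165 × 0.8 = 132 analyzed nurses per arm.

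- T1 difference in change: SE = √(4(1 − r)/132) = 0.123; 0.4/0.123 = 3.25; power 90%.
- Slope, 0/1/2, sustained effect: SE = √(2(1 − r)/(2 × 132)) = 0.0615; 0.20/0.0615 = 3.25; power 90%. The two ratios are equal for any r.
- Slope, months, sustained effect: SE = √(2(1 − r)/(42 × 132)) = 0.0134; 0.0381/0.0134 = 2.84; power 81%.
- Slope, T1-only effect: rejection rate 5% with 0/1/2 and 11% with months, the latter mostly with the wrong sign. The T1 contrast keeps 90%.
- Slope, fading to 0.2: power 37% with 0/1/2 and 19% with months, against 90% for the T1 contrast.

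**4. Categorical time.** The two coefficients are differences in change from baseline to T1 and to T2. In randomized arms each has the standardized difference at its visit as its expectation. If both are tested at 0.05, the chance of at least one false positive is 1 − 0.95² = 9.75% if independent, 9.1% at correlation 0.5 and 7.8% at correlation 0.8. Correlation 0.5 is what the shared baseline produces when all visits are equally correlated.

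**5. Baseline adjustment.** In units of the person-level outcome variance, a change score has variance 2(1 − ρ) and a baseline-adjusted score 1 − ρ². The saving is (1 − ρ)/2. At ρ = 0.5 that is 1.00 against 0.75 (25%); at ρ = 0.8 it is 0.40 against 0.36 (10%). The documents give no ρ, so both values are assumptions.

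**The case against.** The strongest reply is that the protocol never says time is linear. It describes discrete visits and an interaction that captures average differences between arms over time, which fits categorical time well. On that reading each coefficient is a valid standardized contrast at its visit. Coding of time, ranking of visits and rules for multiple testing are often left to an analysis plan, which is not shown here. That stands as far as it goes: silence on coding alone would not be a finding. But the protocol does more than stay silent. It publishes an interpretation rule for a single coefficient, and that rule is wrong for linear time and does not pick out a coefficient for categorical time. A pre/post coding of 0/1/1 with a sustained effect would give 0.40 from one coefficient, but the protocol does not mention such a coding, and a T1-only effect would then give 0.20.

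A reader might infer more than the documents support:

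- **That the reported effect will be halved or will vanish.** This needs linear time, and vanishing also needs the effect to be lost completely by T2. Partial fading to 0.2 gives 0.10 with coding 0/1/2.
- **That halving means lost power.** With coding 0/1/2 and equal correlation the standard error halves too. The 0.038 is a figure per month and should not be set beside 0.4 without converting it.
- **That the sponsor will test both visits and choose the better one.** No passage says so. The 8% to 10% is what two unranked tests would cost.
- **That T1 is already the primary visit.** Counting attrition to post-treatment suggests it but does not declare it.
- **That a difference in change is an error.** It is a valid estimator; baseline adjustment is a gain in efficiency.

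**Conclusion.** The point holds in a conditional form. The sentence equating the treatment*time coefficient with Cohen's d cannot stand with three visits. Under linear time it names a quantity that is not comparable with the planned 0.4, and a T1-only effect would be missed. Under categorical time it leaves two contrasts without a ranking, with a false-positive chance of about 8% to 10% instead of 5% if both are tested.

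The linear-time coefficients rest on balanced data and random intercepts. The power figures also rest on equal correlation between visits and constant ward effects, and the error rates on an assumed correlation between the two tests. Which of the two faults applies depends on a coding that the protocol does not state.

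The same reasoning reaches the client outcome at 0, 3 and 6 months: a sustained 0.4 would be 1.2/18 = 0.067 per month, and a T1-only effect 0.

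**What to change.** Before the analysis:

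1. Enter time as categorical.
2. Name one primary contrast for the 8-item ADL MAINtAIN score. The sample size section suggests the arm difference at T1; the sponsor should confirm this or name T2. The documents do not show whether data collection has finished. If it has, the choice should be recorded before any results by arm are seen.
3. Estimate that contrast with adjustment for the baseline score, or with the baseline means constrained to be equal across arms. In person-level variance, adjustment is at least as efficient as the difference in change.
4. Treat the other visit as secondary.
5. Define d as the primary contrast divided by a named SD, for example the pooled baseline SD.
6. Replace the sentence that equates the interaction coefficient with Cohen's d by that definition.

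The cost is wording and model syntax. No visit, measurement or participant is added.

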#### Economic evaluation

The economic evaluation will evaluate the cost-effectiveness of the SELF-program compared with care as usual over 6 months. The principal analysis will be the incremental cost per quality adjusted life year gained from the societal perspective using the EQ-5D-5L to calculate QALYs as recommended by the Dutch Healthcare Institute [45]. This will be calculated as the mean cost difference between the SELF-program and care as usual divided by the mean QALY difference to give the incremental cost-effectiveness ratio (ICER). Use of QALYs as a generic health outcome measure allows policymakers to compare cost-effectiveness results across different sectors to guide resource allocation decisions. Unit costs will be taken from the Dutch Manual for Costing in Economic Evaluations [49] and other standard published sources. The cost of the SELF-program will also include the costs related to the external actor, who is hired to guide the role-play session.

Estimates for mean total costs and QALYs’ incremental between the SELF-program compared with care as usual over 6 months will be derived using regression analysis to control for differences in baseline utilities and costs, as well as relevant stratification variables. A secondary analysis will include the cost per point change in the primary outcome measure (GARS-4) gained of the SELF-program compared with care as usual over 6 months. Where necessary, analyses will take into account clustering at the nursing home care level via random intercept models. Regression analysis will also be used in the secondary cost-effectiveness analysis to control for potential imbalances in baseline GARS-4 values and stratification variables. To quantify uncertainty around cost-effectiveness results, non-parametric bootstrap methods will be used and 95% bias-corrected and accelerated bootstrap confidence intervals will be calculated for the mean total cost and QALY/GARS-4 incremental estimates. The bootstrap replications will also be used to construct cost-effectiveness planes and cost-effectiveness acceptability curves, from which the probability that SELF-program is cost-effective compared to care as usual at 6 months of the trial will be computed for a range of values of the willingness to pay thresholds based on current recommendations [45].

In the event of considerable proportions of missing economic outcome data, the use of multiple imputation techniques will be explored to handle missingness. We will also subject the results to additional sensitivity analyses. For example, we will explore the cost-effectiveness and cost-utility of SELF-program compared with care as usual based on: a health and social services cost-perspective (including only healthcare costs); the complete cases (participants with complete data for all outcomes).

### Process-evaluation

Both quantitative and qualitative methods will be used to analyze the data obtained from the process evaluation. Quantitative data on reach, dose delivered, dose satisfaction and mechanisms of impact will be analyzed using descriptive and comparative statistics using SPSS software. Qualitative data obtained from the focus group interviews will be transcribed verbatim, anonymized and analyzed using Nvivo Software [53] using a predefined thematic coding scheme related to concepts addressed in the process. We aim to analyze the process evaluation data prior to the effectiveness and cost-effectiveness outcomes in order to prevent biases in interpretations of results [50].

## Discussion

The SELF-program is a nursing program based on the principles of Function Focused Care, and aims to improve activity stimulation behavior of nursing care professionals in long-term care services, and with that optimize levels of self-reliance in ADL in geriatric clients. The intended cluster-randomized trial in nursing home care described in this paper, aims to provide insight into the program’s effectiveness and cost-effectiveness, and is supplemented with a thorough process-evaluation to examine the program’s feasibility regarding implementation, its mechanisms of impact and contextual factors.

Recent reviews show that current FFC-based programs across various care settings show mixed effects on improving either care professionals’ FFC-enhancing behavior and clients’ engagement in physical and functional activity [25, 54]. Based on suggestions from these reviews and synthesized findings from process evaluations of the previously developed and tested Dutch FFC-based programs, several lessons and implications have been formulated to optimize future programs and develop an advanced generic FFC-program (SELF) accordingly [31]. In brief, these implications include: 1) the development of a program applicable to a variety of care settings which allows for setting specific tailoring, 2) addressing all FFC-components in conjunction, 3) incorporating a comprehensive interactive educational component, 4) incorporating of an extended integrated theory of behavior change, and 5) improvement of managerial support by ensuring sufficient time and staff resources.

A key principle of FFC-based programs is the holistic approach in changing nurses’ care and consequently clients’ activity behavior [24]. Although current Dutch programs are based on the principles of the FFC-philosophy or similar care concepts, not all aspects considered relevant are addressed in conjunction. Multicomponent interventions are considered most promising in enhancing the functional abilities of clients [54], thereby building on a comprehensive and interactive educational component as a core element to facilitate staff training [55]. To address the uniformity, which seems to be lacking given the wide variety of available interventions nationally and internationally, a generic function focused care program was developed to be applicable in long-term care. This generic nature does not imply the absence of setting-specific tailoring or tailoring to the needs of participants. In fact, a key implication addressed in the SELF-program is to tailor the content to the setting the program is to be carried out in, e.g. home care, or the knowledge level and willingness of participants to practice FFC within the framework of the developed generic approach [56]. Tailored and interactive educational strategies, including motivational and encouraging techniques, are considered promising interventions when aiming for geriatric clients to become more empowered [57]. This way, the demand for developing more uniform interventions is met – given FFC-programs respond to a topic that is relevant in all nursing care settings – as well as need to create greater cognitive processing in participants by the application of tailoring [58].

This study set up has several strengths. First, the SELF-program has been developed within the cyclic framework of the Medical Research Council, which addresses the systematic development, feasibility testing, evaluation and implementation of complex interventions [50]. After the development of the SELF-program, taking into account lessons learned and implications gathered from process evaluations of previous Dutch FFC-based interventions, the SELF-program was feasibility tested in one nursing home ward. The SELF-program was considered feasible in practice and valuable adaptations have been applied prior to the onset of the intended CRT in nursing home care. Another strength, and with that building on implications from previous work, is the incorporation of a more integrated theory of behavior change. More specifically, the SELF-program incorporates a thorough sequential dual behavior change process in which first attempts are made to change the behavior of nurses before they are enabled to improve client’s activity behavior. Although the FFC-philosophy includes behavior change determinants as mechanisms to alter care professionals behavior, recent work questions whether addressing these determinants is sufficient to bring about change. Consequently, it is advocated to include a broader spectrum of behavior change determinants by using integrative behavior change models such as the one addressed in the SELF-program [32]. In addition, we adhere to the suggestions addressed by Lee and colleagues and Verstraten and colleagues to conduct thorough evaluations of FFC-based programs and to use research methods aimed at producing more rigorous burdens of proof [25, 54]. Limitations of the study include the subjective approach of data-collection, i.e., using self-report questionnaires. However, objective measures such as researcher-based observations or videos taken from daily practice may interfere with the client’s and care professionals privacy, for example when examining stimulation behavior and self-reliance in care activities related to personal cleanliness. In line, although it is common in healthcare to collect data from clients with psychogeriatric complaints by their first responsible caregiver – given they have direct and frequent contact to the client in question – we have opted to collect data from all nursing home clients by their primary responsible caregiver. This implies that data from clients with somatic backgrounds will also be collected by their first caregiver, although they might be self-capable to provide the data. However, to address the uniformity of data-collection, and given somatic and psychogeriatric complaints commonly co-occur in Dutch institutionalized care, this approach was considered most feasible. Last, the follow-up period chosen in the CRT is based on practical and financial considerations. However, regarding the outcomes assessment in geriatric clients, i.e., self-reliance in daily activities, it is debatable whether a follow-up period of 6 months is long enough to detect changes. Since the SELF-program assumes that primarily a behavior change is required in care professionals, its translation into adequate changes in day-to-day care practice and subsequently client’s self-reliance may – if any – occur beyond this time period.

The SELF-program offers an advanced and holistic approach to improve activity stimulation behavior of nursing care professionals in long-term care services, and with that optimize levels of self-reliance in ADL in geriatric clients, for a variety of nursing care settings. The results of studies as described in the research protocol are expected to be available from end 2022 onwards. A similar trial is proposed for the home care nursing setting to demonstrate the effect, cost-effectiveness and feasibility of the SELF-program in another long-term care setting.

